# Study objectives

The study is a RCT to compare the treatment effect and safety aspects of vaginal 1% Chlorhexidine gluconate (CHG) versus oral Fluconazole® (FLZ) for recurrent vulvovaginal candidiasis (RVVC).

## Primary objective

To analyze if daily vaginal application of 8 ml of Hibitane® for one week and thereafter once a week for another 11 consecutive weeks is at least as effective as fluconazole 150 mg capsules every third day for the first three doses and thereafter 150 mg once a week for another 11 consecutive weeks regarding treatment- and prophylactic efficacy for recurrent vulvovaginal *Candida albicans* infection*.*

## Secondary objective(s)

1. To analyze adverse events
2. To analyzed clinical symptoms and findings
3. To study the effect on vaginal microbiome of lactobacillus before and after treatment and prophylaxis with CHG for RVVC.
4. To evaluate the event of relapses during and after the prophylaxis treatment
5. To investigate if CHG has toxic effect on the vaginal epithelial cells.
6. To analyze vaginal biofilm formation before and after treatment and prophylaxis with CHG and FLZ for RVVC.

## Primary endpoint (variable)

The proportion of women in each group that has negative vaginal cultures for *Candida albicans* 1 week after active treatment.

## Secondary endpoint (variables)

1. The proportion of women in each group that has negative vaginal cultures for *Candida albicans* at 3 months’ follow-up after prophylactic treatment and at 6 months’ follow-up after the observational phase of the study.
2. Analysis of proportion of women with adverse events (AE) across treatment arms. The AEs will also be reported in descriptive terms and summarized for each treatment arm.
3. Proportion of women with symptom score > 2. Each symptom of typical discharge, itching, dryness of the skin/mucosa, burning and pain will generate 1 point of a composite index (range 0-5).
4. Proportion of women with examination score >2. Each finding of redness skin/mucosa, typical discharge, dry skin/mucosa, fissures skin/mucosa, visible candida hyphae in the microscope will generate 1 point of a composite index (range 0-5).
5. Proportion of women with reduced vaginal lactobacilli content in vaginal smears measured by a semi-quantitative method as normal or reduced quantity.
6. Proportion of women with relapse of *Candida albicans* infection between end of treatment and end of prophylactic treatment (1week post treatment to 3 months’ follow-up) and between 3- and 6 months’ follow-up after end of prophylactic treatment.
7. Proportion of women with possible toxic effect on the vaginal epithelium, defined as disruption and/or inflammation of the epithelial lining, analyzed from vaginal biopsies before and after treatment and prophylaxis.
8. Further analysis of mucosa inflammatory mechanism (histopathology and immunohistochemistry) and biofilm formation during and after treatment and prophylaxis, analyzed from vaginal biopsies. The methods for these *in vitro* exploratory analyses are not yet decided on.

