# Subject selection

## Inclusion criteria

To be included in the study, subjects must meet the following criteria:

- 18-50 years of age
- A history of > 2 candida infections the last year
- Symptoms of acute vulvovaginal candida infection
- Culture verified infection with *Candida albicans*
- Adequate contraceptive method
- Able to understand oral and written information in Swedish
- The subject has given written consent to participate in the study

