### Secondary endpoints (variables)

1. The secondary endpoint of treatment efficacy is the proportion of women in each group that has negative vaginal cultures for *Candida* albicans at 3 months’ and 6 months’ follow-ups, after end of prophylactic treatment. The cultures will be analyzed as described under 8.1.1.
2. Adverse events will continuously be registered during the study. The participants can fill out any AE in a web based digital weekly diary but also contact the research midwife when needed. AEs will be described and summarized and compared between treatment arms regarding proportion of women with AE.
3. A symptom and examination score (composite index 0-5) will be measured first at baseline/inclusion and then at 3 follow-ups; 1 week after treatment, 3 months’ follow-up after prophylactic treatment and at 6 months’ follow-up. The investigator will ask the participant for common symptoms of RVVC (typical discharge, itching, dryness of the skin/mucosa, burning and pain). Each present symptom will generate 1 point of the composite index (range 0-5). During the gynecological examination performed at inclusion and at each follow-up, typical clinical findings (redness skin/mucosa, typical discharge, dry skin/mucosa, fissures skin/mucosa, visible candida hyfae under the microscope) will be registered in the CRF. Each finding will generate 1 point of the composite index (range 0-5). The proportion of women in each treatment arm with symptom- and examination score >2 for both the will be used for statistical analyses.

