***Statistical methods:***

Analysis for differences over time for treatment efficacy, AEs, symptom- and examination score, impact on vaginal lactobacilli and relapses will be analyzed for all randomized patients (i.e. intent-to-treat ITT). Additionally, we will also examine efficacy for the per-protocol (PP) population. Four time points will be used to study the efficacy (proportion of participants with negative cultures for *Candida albicans*) in each treatment arm (baseline, 1w post-treatment, follow-up 3 and 6 months). We will examine the difference in means, proportions and median values using 95% confidence intervals (CI). The CI interval will be computed using 1) for a proportion in one sample and 2) logistic or multinomial logistic regression analysis.

Differences in baseline characteristics between the CHG and FLZ groups will be analyzed with Chi2 for categorical data, Mann Whitney U test for ordinal data, or t-test for continuous data to examine potential selection bias at randomization. Differences in drop-out rates across treatment arms will also be analyzed using Mann Whitney U test.

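### Cutting the 0-5 symptom and examination scores at >2 gives up power on two secondary endpoints; testing the full score with the Visit 2 score as covariate would need no new data

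*Protocol*

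**What the plan says.** The secondary endpoint list, under the study objectives, gives "Proportion of women with symptom score > 2" and "Proportion of women with examination score >2". Each score is a count of five items. The synopsis and section 10.2.1 (Statistical methods) repeat the cut.

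Section 8.1.2 sets the timing: "A symptom and examination score (composite index 0-5) will be measured first at baseline/inclusion and then at 3 follow-ups". It also fixes the form in which the scores are analysed: "The proportion of women in each treatment arm with symptom- and examination score >2 for both the will be used for statistical analyses". A word is missing from that sentence, but the quantity named is a proportion above 2.

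The inclusion criteria ask for "Symptoms of acute vulvovaginal candida infection". They set no minimum symptom score and no criterion on the examination score.

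Section 10.2.1 plans "Analysis for differences over time for treatment efficacy, AEs, symptom- and examination score" among other outcomes, and adds "We will examine the difference in means, proportions and median values using 95% confidence intervals (CI"). Its regression method is "logistic or multinomial logistic regression analysis". It does not say which variables get means or medians, or how the baseline score enters a model.

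**The concern.** These two endpoints answer the secondary objective on clinical symptoms and findings. The cut reduces six ordered values to two, and its definition makes no reference to the score at Visit 2, although that score is collected.

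Three consequences follow:

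- A woman who enters with 1 or 2 points is already on the favourable side of the cut. She can cross it by worsening, but not by improving.
- A woman who falls from 5 to 3 stays on the unfavourable side and is counted with those who did not change.
- With 30 women per arm, and false-discovery-rate control across all secondary outcomes, there is little information to spare.

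What is at stake is sensitivity. In a trial that asks whether chlorhexidine is at least as good as fluconazole, an insensitive comparison makes the arms look alike more often than the data warrant.

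**Working it through.** **The plan's own figure.** No power is stated for either score. The only sample size concerns the culture endpoint, and it reproduces at one-sided 5%: n per arm = 2 × 0.86 × 0.14 × (1.645 + 1.282)² / 0.30² = 0.2408 × 8.567 / 0.09 = 22.9, so 23 per arm and 46 in total. The present point leaves that figure untouched.

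**Inputs.** From the protocol: 30 per arm, scores 0-5, cut at >2. Assumed, because the protocol gives no distribution: follow-up scores 0 to 5 in one arm at 30/25/20/13/8/4%, so 25% above 2; a common odds ratio of 3; baseline correlation 0.3-0.5; two-sided 5% before any multiplicity adjustment.

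**Information kept by the cut.** For a proportional-odds comparison, information is proportional to 1 minus the sum of cubed category shares.

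- Two categories: 1 − 0.75³ − 0.25³ = 0.5625.
- Six categories: 1 − (0.027 + 0.015625 + 0.008 + 0.002197 + 0.000512 + 0.000064) = 0.9466.
- Ratio: 0.5625 / 0.9466 = 0.594.

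A second approximation treats the score as a dichotomised normal variable. Its efficiency is φ(c)²/[q(1 − q)], where q is the share above the cut: 0.64 at q = 50%, 0.49 at 20% and 0.34 at 10%. Multiplied by 30, that is worth about 19, 15 and 10 women per arm.

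**Power of the >2 comparison.** The odds at 25% are 1/3. An odds ratio of 3 leads to 50% in one direction (odds 1) and 10% in the other (odds 1/9).

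- 25% v 50%: null SE = √(2 × 0.375 × 0.625 / 30) = 0.125; alternative SE = √((0.1875 + 0.25) / 30) = 0.1208; (0.25 − 1.96 × 0.125) / 0.1208 = 0.04, power about 52%.
- 25% v 10%: null SE = √(2 × 0.175 × 0.825 / 30) = 0.0981; alternative SE = √((0.1875 + 0.09) / 30) = 0.0962; (0.15 − 1.96 × 0.0981) / 0.0962 = −0.44, power about 33%.

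**Power of the full score, by simulation under the same assumptions.**

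| Shift | >2 | Full score (rank test) | Rank ANCOVA with baseline |
|---|---|---|---|
| towards higher scores | 52% | 65% | 67-76% |
| towards lower scores | 33% | 61% | 65-69% |

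Type I error was about 4.5%. The adjusted figures move by a point or two with the assumed baseline distribution: a repeat with baseline scores at 2/8/15/25/30/20% and 5,000 trials per scenario gave 68-74% and 66-71%.

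**A different model.** Here the score is the sum of five correlated yes/no items, with item prevalence 20% v 40% at follow-up and 30 per arm. Power was 54-68% for >2, 73-88% for the full score (Mann-Whitney) and 75-90% for ANCOVA with baseline. In this model most of the gain, about 17-23 points, comes from keeping the full score; baseline adjustment adds about 0-6.

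**Women at or below 2 at entry.** If the five items were independent, the share is P(X ≤ 2) with X binomial(5, mean/5): 50% at a baseline mean of 2.5, 32% at 3.0, 16% at 3.5 and 6% at 4.0. Of 30 women per arm, that is between about 2 (0.06 × 30) and 15 (0.50 × 30). Nothing in the protocol narrows this range.

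**The case against.** The endpoint can be read as the prevalence of a substantial burden, at least three of five items, at a given visit. So read, it need not refer to baseline, and it gives a plain percentage that clinicians understand. The index adds unlike items (pain, dryness, visible hyphae), so a fixed threshold is a recognised choice. Women who enter low are not inert either: they cross the cut if they worsen, which is relevant at weeks 12 and 24. An ordinal model adds a proportional-odds assumption, and a common odds ratio is the condition that favours it. All of this stands, and it is why the point is an improvement and not an error.

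A reader might also infer three stronger things that the document does not support.

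- That baseline is excluded from the analysis. Section 10.2.1 plans a comparison over time that names both scores, so the role of baseline is unspecified. Model detail may properly sit in the SAP, which is not shown.
- That unchanged women are counted as successes. The protocol never gives a score of 2 or less that label, and unchanged women with 3 to 5 points count as above 2.
- That the result is tilted towards chlorhexidine. Allocation is randomised 1:1, so low-scoring women are balanced in expectation. No non-inferiority limit is set for the scores, and the planned confidence intervals would show low precision as width.

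The SAP argument does not reach the cut itself. Section 8.1.2 names the proportion above 2 as what the analyses will use, and the general mention of means, medians and multinomial regression does not assign any of them to these scores.

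**Conclusion.** The point holds as a low-severity improvement. The protocol itself chooses the cut at >2, and its endpoint definition leaves out a Visit 2 score that is already collected. The harm is dilution and lost power, with no bias towards one arm. Under the assumed distribution and an odds ratio of 3, the cut costs about 13 points of power against the full score (65 − 52) in one direction and about 28 (61 − 33) in the other, before any baseline adjustment. The size depends on the assumed distribution, correlation and effect; what is common to all scenarios run is that the full score has more power. The share of women who start at or below 2 cannot be derived from the protocol. Two of eight secondary endpoints are affected. The primary endpoint and the sample size are not.

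**What to change.** In the synopsis, the secondary endpoint list, section 8.1.2 and section 10.2.1, state that each 0-5 score is tested at each follow-up as an ordinal outcome, by a proportional-odds model or rank ANCOVA, with treatment and the Visit 2 score as covariates. Keep the proportion above 2 per arm, with its 95% confidence interval, as a descriptive summary.

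The change needs no new data, visits or participants. The cost is that the tested effect becomes an odds ratio or rank difference in place of a simple percentage, and that the proportional-odds model, if chosen, brings its own assumption.

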# Study design and procedures

The study was originally planned to start in March 2021, but the start of the study has been postponed due to the Covid -19 pandemic. The study will not start until the pandemic is under control and when there are no risks for participants to travel and visit Danderyd hospital. Estimated study start will be May 2021, when the Covid -19 vaccination is carried out in the major part of the Stockholm population. Caution to avoid infection transmission will be carried out and recommendations and regulations from the Swedish Health Authority and from Region Stockholm will be followed.

## Overall study design

The study is a 6 months clinical Phase II trial to compare if 1% chlorhexidine gluconate vaginal cream (Hibitane®) is at least as effective and safe as fluconazole (reference treatment) for culture-verified recurrent vulvovaginal candidiasis. The study is a randomized open non-inferiority trial with parallel treatment groups. The trial is not possible to blind for neither participants nor investigators due to the differences between study treatments. There is low risk of bias since the primary outcome variable is objective (negative vaginal culture for *Candida albicans*).

The rational for the study is to find an alternative treatment to fluconazole for RVVC with high tolerability and without cytotoxic effect on epithelial cells and negative impact on the vaginal microbes.

The participants will be randomization to;

- Investigational medication with Hibitane® vaginal cream 8 ml every night for a week and then prophylactic treatment with 8 ml/week for another 11 weeks

or

- Reference treatment with Fluconazole® 150 mg (oral capsule) every 3 days for the first 3 doses, then prophylactic treatment with 150 mg/week for another 11 weeks

Please see section 7 for more details on randomization and study treatments.

Figure 1 Study design

| **Visit** | **1** | **2** | **3** | **4** | **5** |
| --- | --- | --- | --- | --- | --- |
|  |  | CHG | Chlorhexidine gluconate  vaginal application  8 ml/w, 11 w | |  |
|  |  | 8 ml/day,1 w  R |  |  | N=30 |
|  |  |  | Fluconazole  oral capsules  150 mg/w, 11 w | |  |
|  |  | FLZ  150 mg/day,1w |  |  | N=30 |
| **Week:** | **-1** | **0** | **1** | **12** | **24** |
|  | Screening | Inclusion/  Baseline  Randomization | Follow-up | Follow-up | Follow-up and end of treatment |

##

## Procedures and flow chart

**Five research visits are planned:**

**Visit 1** Screening – oral and written study information, signing of informed consent, vaginal culture for Candida albicans and chlamydia/gonorrhea (PCR test). 45 min.

**Visit 2** Inclusion (baseline), within 1 week after Visit 1. Control for inclusion/exclusion criteria, randomization to study medication after positive culture for *Candida albicans* and negative chlamydia/gonorrhea (PCR test) – health survey, control of concomitant medications, examination, vaginal biopsies, pregnancy test and control of adequate contraceptive methods to avoid pregnancy throughout the study. 1 h.

**Visit 3** 1 week (+2 days) after completed treatment. Control of AE, culture for *Candida albicans* and examination (no biopsies). 30 min.

**Visit 4** After 12 weeks (+ 1 week) from inclusion when prophylactic treatment is completed. Control of AE and relapses, culture for *Candida albicans* and examination, vaginal biopsies. 45 min.

**Visit 5** Follow-up 6 months (+ 1-2 weeks) from baseline/inclusion. Control of AE and relapses, culture for *Candida albicans* and examination (no biopsies). End of study. 30 min.

A weekly web-based dairy (eCRF (Entermedic)) will be used for follow-up of treatment

compliance, efficacy and adverse events. A personal link will be sent via e-mail every week

from week 2-24. During the prophylactic treatment (Visits 2-3) and during the observational

phase of the study (Visit 4-5), the participants are asked to report any suspicious relapses in

the dairy and contact the research midwife if needed. They will also receive equipment for

vaginal cultures that can be used for self-sampling at home to detect true relapses. In case of

positive cultures for *Candida albicans*, they will be offered the same medication as previously

used in the study if the treatment was effective and no adverse events occurred. Otherwise,

an individual treatment option will be used.

Table 1 Flow chart

| **Procedure** | **Visit 1**  Screening  Week -1 | **Visit 2**  Baseline/  inclusion  Week 0  (within 1 w from Visit 1) | **Visit 3**  Follow-up  Week 1  (treatment)  (+2 d) | **Visit 4**  Follow-up  Week 12  (prophylactic phase)  (+1 w) | **Visit 5**  Follow-up  Week 24  (observational phase)  (+2 w) |
| --- | --- | --- | --- | --- | --- |
| Incl/exclusion criteria | √ | √* |  |  |  |
| Informed signed consent | √ |  |  |  |  |
| Medical health questionnaire/ concomitant medications |  | √ |  |  |  |
| Randomization |  | √ |  |  |  |
| Vaginal culture  Candida | √ |  | √ | √ | √ |
| PCR test**  Clamydia/  Gonorrhea | √ |  |  |  |  |
| Pregnancy test |  | √ | √ |  |  |
| Symptom score |  | √ | √ | √ | √ |
| Examination score |  | √ | √ | √ | √ |
| Microscopy  lactobacilli |  | √ | √ | √ | √ |
| Vaginal biopsies |  | √ |  | √ |  |
| Instructions for handling the investigational product(s) |  | √ |  |  |  |
| Adverse Events (AE & SAE) |  |  | √ | √ | √ |
| Study end |  |  |  |  | √ |

**if positive culture for Candida albicans*** Chlamydia/gonorrhea test will be repeated in case of new partner during the study

##

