## Dose and administration

1. Hibitane® is a cream and will be applied vaginally by the help of a 10 ml plastic syringe (Braun, Melsungen, Germany, CE 0123), provided to the participants randomized to Hibitane®. During the first week of treatment 8 ml is used every night at bedtime and thereafter 8 ml will be used at night once a week for 11 consecutive weeks. The dose of 8 ml is considered an adequate to be applied in the vagina for achieving treatment effect. Most of the cream will stay in place, but a small portion will leak and a genital pad is recommended. Dose changes or withdrawal of the medication will be considered in case of AE.
2. Fluconzole® oral 150 mg capsules will be used every 3 days for the first 3 doses, thereafter as prophylactic treatment with 150 mg/week for another 11 consecutive weeks. The fluconazole regime serves as the reference medication normally used for recurrent vulvovaginal candidiasis according to international recommendations and FASS. Fluconazole can be taken regardless of food intake. Dose changes or withdrawal of the medication will be considered in case of AE.

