# Statistics

## Analysis population

The study is a RCT controlled non-inferior trial with 60 women randomly assigned to either vaginal chlorhexidine gluconate (N=30) or oral fluconazole (N=30). Baseline plus 3 follow-up visits (baseline/inclusion, 1 week, 3 months and 6 months) are planned.

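### The protocol sets the primary-endpoint culture at two non-overlapping times: one week after treatment ends (text) and Week 1 from baseline (Figure 1 and Table 1)

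*Protocol*

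**What the plan says.** The visit list in section 5.2 schedules Visit 3 "1 week (+2 days) after completed treatment". The primary endpoint in section 4.3 is the proportion with "negative vaginal cultures for *Candida albicans* 1 week after active treatment". The Synopsis, section 8.1.1 and section 10.2.1 use the same anchor.

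The schedule says something else. Table 1 (section 5.2) heads the Visit 3 column with "Week 1 (treatment) (+2 d" in brackets. Figure 1 (section 5.1) puts Visit 3 at week 1 on a row running -1, 0, 1, 12, 24, where 0 is baseline and randomization. That scale counts from inclusion, since Visit 4 is "After 12 weeks (+ 1 week) from inclusion when prophylactic treatment is completed". Section 10.1 states: "Baseline plus 3 follow-up visits (baseline/inclusion, 1 week, 3 months and 6 months) are planned".

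On dosing, section 7.2 says of CHG: "During the first week of treatment 8 ml is used every night at bedtime". Weekly applications follow for 11 weeks. Fluconazole (FLZ) is given as three doses three days apart, then weekly for 11 weeks.

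Two further statements bear on Visit 3. Section 9.6 requires two pregnancy tests, the second before prophylaxis begins, and Table 1 places that second test at Visit 3. Figure 1 draws the weekly phase as starting at Visit 3.

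**The concern.** A course that fills the first week is not finished until about the end of that week. A visit one week after completion and a visit at Week 1 from baseline are therefore different visits. The first measures clearance some days after the initial course, and the second measures it as the course ends. This is the trial's only primary endpoint, and the non-inferiority conclusion depends on it.

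The same visit also supplies the 1-week symptom score, examination score and lactobacilli assessment, and it starts the first relapse period (sections 4.4 and 8.1.2). All of these move with it.

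There is a second, conditional concern. CHG is an antiseptic placed at the site that is swabbed. If residue from a recent application suppresses growth in culture, a swab taken soon after a dose could read negative in a woman who has not cleared the infection. That would favour CHG in the comparison.

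**Working it through.** **Plan's own figure.** The plan gives no day count to reproduce. Its sample size for this endpoint is reproduced with a one-sided 5% level: (1.645 + 1.282)² × 2 × 0.86 × 0.14 / 0.30² = 22.9, so 23 per group and 46 in total. Nothing in this point changes that figure.

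**Inputs.** CHG on seven consecutive nights and FLZ in three doses at 3-day spacing (section 7.2); Visit 3 window of +2 days (section 5.2); Week 0 = baseline (Figure 1, Table 1). The protocol does not number the day of first dose, so day 0 and day 1 are both tried.

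**Formulas.** Last initial dose L = first-dose day + 6, in both arms. Schedule window = day 7 to 7 + 2. Text window = L + 7 to L + 9.

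| | First dose day 0 | First dose day 1 |
|---|---|---|
| CHG nights | 0-6 | 1-7 |
| FLZ initial doses | 0, 3, 6 | 1, 4, 7 |
| L | 6 | 7 |
| Visit 3 by Figure 1 and Table 1 | days 7-9 | days 7-9 |
| Days after last nightly CHG | 1-3 | 0-2 |
| Visit 3 by visit list and endpoint | days 13-15 | days 14-16 |
| Days after last nightly CHG | 7-9 | 7-9 |
| Difference between window starts | 13 - 7 = 6 | 14 - 7 = 7 |

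The windows do not overlap in either column. A gap of 0 means the same calendar day. As CHG is applied at bedtime, a daytime swab would then come before the seventh application.

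**Recent CHG dosing under the later window.** The protocol does not fix the day of the first weekly dose. Assume it falls k days after the last nightly dose, with k from 1 to 7. Count weekly doses on days before the swab:

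- k = 7: none before a swab at L + 7 (last dose 7 days earlier); one before a swab at L + 8 (last dose 1 day earlier).
- k = 2 to 6: one before every swab in the window.
- k = 1: one before L + 7 or L + 8; two before L + 9 (last dose 1 day earlier).

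So a CHG participant has usually had one weekly application before the swab (range 0-2), and the latest vaginal dose was 1-7 days earlier. Moving to the later window does not by itself remove recent dosing.

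**Pregnancy test and Figure 1.** Within the same range of k, a test at Visit 3 comes before any day with a weekly dose only when k = 7 and the visit is on the first day of the window. Otherwise weekly dosing would have to be held until the visit, which the text does not say. Both items fit the Week 1 reading more easily, and so pull against the endpoint definition.

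**The case against.** **The table label may be shorthand.** Its bracketed word could mean one week after treatment, and the 1 week in section 10.1 can be read either way, since section 10.2.1 says post-treatment. The section 10.1 point stands. The table reading is strained: the other two follow-up columns name the phase just ended and count their weeks from baseline.

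**A reader might infer that carry-over occurs, affects only the CHG arm, and therefore biases the trial towards non-inferiority.** The documents do not support that. They contain no data on residue or growth inhibition in culture for either drug. FLZ is oral, but the protocol expects it to clear vaginal *Candida*, and its third dose falls on about the same day as the last nightly CHG. What stands is that CHG is applied directly at the swab site, so the possibility deserves a safeguard.

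**A reader might also put a size on it.** If 10-25% of true CHG failures read negative and true success is 56% (86% less the 30-point margin), observed success is 0.56 + 0.44 × 0.10 = 0.604 to 0.56 + 0.44 × 0.25 = 0.67, or 4-11 points. The 10-25% has no anchor in the protocol, so this is not an estimate of bias.

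**The objectivity statement does not claim what it might seem to.** Section 5.1 says "There is low risk of bias since the primary outcome variable is objective", directly after explaining that blinding is impossible. It answers open-label bias and makes no claim about antiseptic residue.

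**Swab order is partly implied.** Weekly CHG is used at night, so on a shared day an ordinary clinic visit comes first. That does not cover a dose taken a day or more before the visit.

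**Some remedies may belong in the SAP.** The SAP is listed as an attachment and was not available. An analysis restricted to in-window swabs may already be there. The SAP cannot, however, change the day on which a swab was taken.

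**Conclusion.** The contradiction holds and should be corrected. The protocol fixes its primary-endpoint visit at days 7-9 in the schedule and at days 13-15 in the visit list and endpoint definitions (14-16 with a day-1 start). The windows do not overlap. The only assumptions are the day number of the first dose and completion of the seven-night and three-dose initial courses as written. The need to correct it rests on this contradiction alone.

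Carry-over remains conditional. It could favour CHG if residue suppresses growth, it could arise under either timing, and the documents allow neither its existence nor its size to be established.

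**What to change.** - Reconcile Figure 1, Table 1, the visit list, section 9.6 and section 10.1 with the endpoint definition, using one day count from first dose for Visit 3. The 1-week secondary assessments and the start of the relapse period should refer to the same count.
- State the order of the Visit 3 swab and the first weekly dose, and reconcile this with the second pregnancy test and with Figure 1. Which order applies is for the trial team to decide.
- Record the date of the last study dose at Visits 3 and 4. The weekly diary does not fully cover this, because its links are sent from week 2.
- Report the primary result also for swabs taken within the defined window, unless the SAP already provides for it.

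The cost is edits to the schedule and one CRF field. No visit is added and the sample size does not change.
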